### Assessment

2.7

At baseline, post and follow-up, balance performance, BBS, EEG, quality of life, fatigue, pain, spasticity and activity- and participation-related parameters will be collected. The following table (Table 7) shows the time schedule of patient enrolment and intervention.

**Table 7 tbl7:** Time schedule.

	Registration	Baseline assessment	Post assessment	Follow-up assessment
Fulfillment of the inclusion criteria	X	12 weeks hippotherapy or 12 weeks treatment as usual		6 weeks treatment as usual
Written declaration of informed consent	X			
Medical clearance	X			
Assignment to the study group	X			
Anthropometric data	X			
Balance assessment/EEG		X	X	X
BBS		X	X	X
Quality of life (MSQoL-54)		X	X	X
Fatigue (FSS)		X	X	X
Pain (VAS)		X	X	X
Spasticity (NRS)		X	X	X
WHODAS 2.0 36-Self		X	X	X
EQUITEDO® (IG only)		X	X	

### Statistical procedures

2.8

The sample size was estimated on the basis of the primary outcome measure, the relevant effect size and the planned statistical test procedures. Statistical results of preliminary study MS-HIPPO showed a large effect in the per-protocol population with a change of 4.61 points in BBS between the IG and CG (95 % CI: .74–7.47, p = .002, N = 41) [11]. As individual-level baseline data were not available, a baseline–post correlation could not be calculated, and the sample size was therefore estimated based on the large empirical effect observed in the MS-HIPPO trial. Sample size was determined with G∗Power (Heinrich Heine University Duesseldorf, Germany, version 3.1.9.7) for the statistical F-test ANCOVA with two groups and five covariates, assuming an effect size of f = .40 (α = .05, 1–β = .80). This resulted in N = 111 (df = 104, actual power = .80), which was inflated to N = 140 to account for an anticipated 20% attrition rate, for the primary analysis model [35], consistent with methodological recommendations in clinical research using the standard factor ( *Nplanned* = 111 ÷ (1 − .20) = 139 ≈ 140), [11,36].

The study represents a confirmatory analysis, but due to the in-depth biomechanical and neurophysiological experimental measurements, the sample size calculation also includes a calculation of an additional sub-sample for the experimental protocol. In addition to the assessments listed in Table 7, they subsequently completed the balance tasks on the force plate and oscillating sensorimotor therapy device at each of the three measurement timepoints (see Table 6). In order to protect the patient collective of the study and avoid increased drop-out due to complex biomechanical and neurophysiological measurement technology, a reduced sample size was calculated on the basis of the effect strength of the preliminary study [11,14]. According to the effect size calculations of the Institute for Medical Statistics and Bioinformatics at the University of Cologne, the mean difference in BBS of 3.07 points (standard deviation (SD) = 1.04) of the IG and CG for a type 1 error rate of α = 1 % and a power of 1-β = 95 %, a required minimum sample size of N = 44 was calculated for the statistical F-test ANCOVA (fixed effects, main effects and interactions, two groups and five covariates) (95 % CI: 1.00–5.14, p = .004) assuming an effect size of f = 1.47 (df = 36, actual power = .95) [11,35]. Based on the ≈40 % drop-out rate of the preliminary study (N = 70) PP analysis (N = 41), a total of 70 patients (2x35) shall be randomized for in depth-biomechanical and neurophysiological measurements (during balance task and balance perturbation task) with a drop-out rate of around 40 %, to ensure a sufficient number of cases for this more extensive analysis [11]. Statistical evaluations will be carried out using the programs IBM SPSS 29 (IBM, Ehningen, Germany), R-Statistics (R Foundation, Vienna, Austria), JASP (JASP Team (2024), JASP (Version 0.19.3) [Computer software]) and Python [37]. Statistical methods for analyzing the primary outcome of change in balance performance after 12 units of therapy (change from baseline) will be covariance analyses (ANCOVA) (95 % confidence interval). The data will be analyzed with regard to an anchor-based approach of the minimal clinically important difference (MCID) of the BBS in individuals with MS (3 points according to Gervasoni et al., [38]. These analyses shall be verified by sensitivity analyses using linear mixed models (LMMs). Via this approach, incorporate fixed and random effects are being calculated to accurately represent non-independent data structures, to capture the change over the duration of therapy and follow-up. Therapeutic facility, gender, age, baseline BBS and EDSS score are included in the calculations as co-variables. This approach accommodates missing data under the missing at random (MAR) assumption, ensuring that all available measurements are included and therefore provide less biased and more robust estimates.

The secondary study endpoints will be examined using descriptive statistical methods. Furthermore, to complement the primary analysis, an analogous ANCOVA will also be performed for secondary study endpoints. For the quality of life questionnaire (MSQoL-54), an MCID of 1.5 and 2.5 points will be applied [39]. Three procedures are applied to analyze the study results: (1) the *modified* intention-to-treat population (*m*ITT), which comprises all registered patients who completed the pre-measurement and serves as the primary analysis set for this investigation. It represents a solution for managing complications as noncompliance or missing outcomes and therefore reflects the practical clinical scenario [40]. (2) The *per protocol* population (PP): This data set contains all patients who completed the study without or with very minor violations of the regulations according to the study program and is considered a sensitivity analysis. It is considered a protocol violation if less than 9 units of hippotherapy were completed. Analyses for primary and secondary endpoints will be conducted for *m*ITT and PP populations, whereas evaluations based on the PP-population will serve as sensitivity analyses. (3) The third data set includes the safety population and considers AEs; it includes patients who completed at least one treatment, as opposed to the treatment they were randomized to receive. Safety data (AEs) are summarized and documented according to type, severity, intensity and correlation [41].

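### The primary sample size of 111 does not follow from its stated inputs: a two-group ANCOVA at f = .40 needs 52, and 111 gives power of about .99 at that effect, not .80

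*Protocol article*

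**What the plan says.** The Statistical procedures section (2.8) gives the calculation as a G*Power run "for the statistical F-test ANCOVA with two groups and five covariates, assuming an effect size of f = .40", with α = .05 and power .80. The result is stated as "This resulted in N = 111 (df = 104, actual power = .80), which was inflated to N = 140", the increase being for 20% attrition (111 ÷ .80 = 139, rounded to 140). The numerator df is not printed.

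The large effect is supported by the preliminary trial, which "showed a large effect in the per-protocol population with a change of 4.61 points in BBS between the IG and CG" (N = 41). The same section later defines the modified intention-to-treat set, "which comprises all registered patients who completed the pre-measurement and serves as the primary analysis set for this investigation", and makes the per-protocol set a sensitivity analysis.

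The primary analysis is an ANCOVA of BBS change from baseline, intervention against control. On covariates the section says: "Therapeutic facility, gender, age, baseline BBS and EDSS score are included in the calculations as co-variables". It also plans a 95% confidence interval and an analysis with regard to a 3-point MCID.

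**The concern.** All the inputs needed to check the sample size are printed, apart from the numerator df. That one follows from the design, because a comparison of two arms has 1. The printed N is more than twice what these inputs require, so at least one stated figure is wrong.

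This is the power statement for the confirmatory endpoint. As written, it tells the reader that 111 evaluable patients give 80% power only for a large effect (f = .40, which is d = .80 for two equal groups). If the test has 1 numerator df, the trial can detect clearly smaller effects, and a null result would say more than the text implies. A reader who repeats the calculation will get 52 and may ask why 140 patients are randomized.

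**Working it through.** **Inputs, all from section 2.8 unless noted.** f = .40; α = .05; target power .80; 2 groups; 5 covariates; even allocation (Design section); attrition 20%. Stated output: N = 111, df = 104, power .80.

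**Formula (the G*Power convention for ANCOVA).** Noncentrality λ = f² × N; error df = N − groups − covariates; power = P(noncentral F > critical F at α). The required N is the smallest that reaches the target power.

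**Step 1: the plan's own figure.** 111 − 2 − 5 = 104, so the printed df shows that two groups and five covariates were entered. The numerator df is then the one free input:

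| Numerator df | Required N | Error df | Power |
|---|---|---|---|
| 1 | 52 | 45 | .806 |
| 2 | 64 | 57 | .803 |
| 5 | 86 | 79 | .800 |
| 9 | 107 | 100 | .803 |
| 10 | 111 | 104 | .802 |
| 11 | 115 | 108 | .801 |

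Only 10 matches the printed N, df and power together. No contrast between two arms has 10 df.

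**Step 2: the correct figure for the stated test.** With 1 numerator df and N = 52, λ = .16 × 52 = 8.32, error df is 45 and power is .806. A normal approximation for d = .80 gives 50 in total. Inflating for 20% attrition, 52 ÷ .80 = 65.

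**Step 3: power at the printed N.** With 1 numerator df, N = 111 and f = .40, λ = .16 × 111 = 17.76, error df is 104 and power is .987.

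**Step 4: other ways to reach 111 with 1 numerator df.**
- Facility as dummy variables (11 or 12 covariates): N stays at 52.
- α = .025: N = 63. α = .01: N = 77.
- Power .95 at α = .05: N = 84.
- f = .20 (f = .40 misread as d): N = 199.
- f of about .27 (more exactly .269): N = 111. This contradicts the printed f = .40.

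**Step 5: what the planned enrolment can detect (1 numerator df, α = .05, five covariates).**
- 20% attrition: 140 × .80 = 112 evaluable; 80% power at f = .267, d = 2f = .53.
- 40% attrition, about the rate section 2.8 reports for the preliminary trial: 140 × .60 = 84 evaluable; 80% power at f = .310, d = .62.

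**Step 6: power for the 3-point MCID, with f = 3 ÷ (2 × SD).** The article gives no SD that can be used directly here, so the range below is an assumption.

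| Assumed SD (BBS points) | f | Power, 112 evaluable | Power, 84 evaluable |
|---|---|---|---|
| 4.3 | .349 | 96% | 88% |
| 4.5 | .333 | 94% | 85% |
| 5 | .300 | 88% | 77% |
| 6 | .250 | 75% | 62% |

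The difference detectable with 80% power is 2f × SD. With 112 evaluable it is .534 × 4.3 = 2.3 points at SD 4.3 and .534 × 5 = 2.7 at SD 5. It passes 3 points at an SD of about 3 ÷ .534 = 5.6. With 84 evaluable and SD 5 it is .619 × 5 = 3.1 points.

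**The case against.** The strongest reply is that the error does no harm. It is conservative, the trial is not underpowered at f = .40, the attrition step is right, and nothing changes in enrolment, type I error or estimator. That stands, and it limits the severity. It does not make the printed figure correct.

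A second reply is that the cause is inferred. This also stands. The numerator df is not printed, and f of about .27 with 1 df would give 111 too. That the stated inputs do not yield 111 needs no inference.

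Third, the power of .987 holds only if f = .40 is the true effect, and the protocol's basis for that effect is a per-protocol result.

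Two stronger readings are tempting, and the document does not carry them:
- A reader might infer that the trial is sensitive to effects below the 3-point MCID, so that a significant result could be clinically trivial. That depends on an SD and an attrition rate that the article does not settle. It fails at an SD above about 5.6 with 112 evaluable, and at SD 5 with 84. Section 2.8 also already plans a 95% confidence interval and an analysis against the MCID.
- A reader might take the 3.07-point difference given for the experimental sub-sample as the preliminary trial's mITT effect and derive f of about .35 to .37. Section 2.8 names no analysis set and no n for that estimate. It labels the accompanying 1.04 an SD, although the printed interval of 1.00 to 5.14 (half-width 2.07, about 2 × 1.04) fits a standard error. The derived f needs an n that the document does not give.

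**Conclusion.** The point holds as an arithmetic error in the conservative direction. For the stated test and inputs the required N is 52, not 111, and the power at N = 111 is .987, not .80. This rests on the printed f, α, number of groups and covariates, and on a two-arm comparison having 1 numerator df. An entry of 10 numerator df is the likeliest explanation, because it matches N, df and power at once, but the sponsor has to confirm it.

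The mismatch between a per-protocol effect size and an mITT primary analysis is a secondary point. It does not affect the arithmetic, but it bears on which effect the restated power should use.

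This should be fixed. It does not threaten the validity of the trial, and statements about power in BBS points remain conditional on the assumed SD and attrition.

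**What to change.** Check the saved G*Power run to see which input was wrong, and re-run with numerator df = 1. Keep N = 140. Replace the power statement in section 2.8 with wording such as: N = 52 suffices for f = .40; about 112 evaluable patients (20% attrition) give 80% power for f = .27 (d about .53); about 84 evaluable patients (40% attrition, as in the preliminary trial) give 80% power for f = .31.

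Tie the restated power to the 3-point MCID or to an estimate from an mITT analysis instead of the per-protocol result. Quote any figure in BBS points together with its assumed SD and attrition rate, as in the table in the working.

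The cost is one re-run and one reworded paragraph, with no change in enrolment or analysis.

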### Intervention

2.4

Hippotherapy will be carried out once a week for 30 min additionally to patients‘ usual physio- and/or pharmacotherapy (1-2x/week). The vibrations of the horse's back and the rhythm of the horse's stride are being utilized to achieve physiological reactions to improve individual balance performance, mobility, muscle strength and an upright sitting position. It will be carried out as a complementary movement-therapeutic approach for study-related purposes and not part of the treatment routine of patients with MS in standard outpatient rehabilitation. Therapies are standardized according to the principles of DKThR and carried out by trained physiotherapists plus state-approved hippotherapy (DKThR)® license [8]. The Intervention manual for hippotherapy (DKThR)® can be found in Appendix A1. The CG will undergo their treatment as usual without additional hippotherapy. Treatment as usual is defined as the continuation of physiotherapy (1-2x/week) and/or pharmacotherapy. The physiotherapeutic treatment aims to improve individual mobility, build up reduced muscle strength, stretch shortened muscles and loosen tense muscles, as well as alleviate pain through massages and/or heat/cold/electrotherapy. This is supplemented by gait and mobility training (everyday mobility) as well as weight-bearing training, improved coordination and balance and stabilization training. The CG will be offered 5 hippotherapy sessions (30-min units once a week) as an incentive after completing the study and to ensure compliance with regard to ethical aspects. Changing inclusion and exclusion parameters will lead to a drop out. A change in medication or participation in another measure (e.g. study, rehabilitation activity) is not permitted during the trial. Participation in less than 9 out of 12 hippotherapy sessions will lead to a drop out. Pregnancy in participants will also lead to a drop out.

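### Seventy sub-sample patients at the stated 40% drop-out leave 42, below the stated minimum of 44, and the 20% and 40% loss rates are never tied to their analysis sets

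*Protocol article*

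**What the plan says.** All the planning figures are in section 2.8 (Statistical procedures) of the protocol article.

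- **Main sample.** The calculation is "for the statistical F-test ANCOVA with two groups and five covariates", "assuming an effect size of f = .40 (α = .05, 1–β = .80". The result is given as "This resulted in N = 111 (df = 104, actual power = .80", "which was inflated to N = 140 to account for an anticipated 20% attrition rate", with the working "111 ÷ (1 − .20) = 139 ≈ 140". The predecessor trial is among the sources cited for this step.
- **Sub-sample** (force plate, perturbation device, EEG). The required minimum is 44, at alpha 1%, power 95% and f = 1.47. The number to randomize is then set: "Based on the ≈40 % drop-out rate of the preliminary study (N = 70) PP analysis (N = 41", giving 70 patients in two groups of 35. The text says this number secures enough cases.
- **Analysis sets.** The mITT set, meaning everyone with a pre-measurement, is primary. The per-protocol set is a sensitivity analysis, and fewer than 9 hippotherapy sessions counts as a protocol violation.
- **Attendance.** Section 2.4 (Intervention) describes the same event differently: "Participation in less than 9 out of 12 hippotherapy sessions will lead to a drop out".

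**The concern.** There are two problems, of different kinds.

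The first is arithmetic. The sub-sample size is presented as sufficient for 44 evaluable patients, but at the drop-out rate given in the same sentence it is not.

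The second is a definition that is missing where it matters. Both calculations cite the same predecessor, yet one uses 20% and the other about 40%. A reader cannot tell whether these are two estimates of one quantity, in which case one is wrong, or estimates of two quantities, in which case both could stand. Section 2.4 makes this harder to settle, because it calls a per-protocol attendance failure a drop-out and does not say whether such patients still have their week-12 BBS measured. If they are not measured, a per-protocol loss becomes a missing primary outcome, and 20% is harder to defend.

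**Working it through.** **Inputs (section 2.8 unless noted).** Main sample: f = .40, alpha .05, power .80, two groups, five covariates, N = 111, error df 104, attrition 20%. Sub-sample: minimum 44, alpha .01, power .95, f = 1.47, 70 randomized, drop-out about 40%. Predecessor: 70 patients, 41 in the per-protocol analysis.

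**1. The plan's own inflation.** N/(1 − d) = 111/0.80 = 138.75, so 139, rounded to 140. This reproduces.

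**2. The predecessor's rate.** (70 − 41)/70 = 29/70 = 41.4%. Describing this as about 40% is fair. The 41 is the per-protocol count, so the rate measures loss from randomized to per-protocol.

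**3. The sub-sample, with the formula of step 1.**
- Expected evaluable: 70 × 0.60 = 42; at 41.4%, 70 × 41/70 = 41. The stated minimum is 44.
- Number needed: 44/0.60 = 73.3, so 74; at 41.4%, 44 × 70/41 = 75.1, so 76.
- Largest drop-out at which 70 still yields 44: 1 − 44/70 = 37.1%.

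**4. What 42 evaluable patients deliver.** I used the noncentral F test for ANCOVA with noncentrality f²N, numerator df 1 and error df N − 2 − 5. Here d = 2f is the group difference in units of the covariate-adjusted residual SD. At alpha .01:

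| Evaluable | d at 80% power | d at 95% power |
|---|---|---|
| 44 | 1.08 | 1.33 |
| 42 | 1.11 | 1.37 |
| 41 | 1.12 | 1.39 |

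**5. The base of 44.** With f = 1.47, alpha .01 and power .95, the same 1-df test needs 15 patients (power .939 at 14, .968 at 15), not 44. The stated error df of 36 also differs from 44 − 2 − 5 = 37. The target is therefore not reproducible as a 1-df test.

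**6. The main sample if 40% were lost.** 140 × 0.60 = 84 (82 at 41.4%). With numerator df 1, f = .40 and alpha .05, power is .952 at 84 and .947 at 82. For reference, N = 111 with error df 104 and power .80 reproduces only with 10 numerator df (power .802). A two-group contrast with 1 df needs 52.

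**7. Sections 2.4 and 2.8 side by side.** For fewer than 9 sessions, section 2.4 says the patient drops out. Section 2.8 says the patient violates the protocol for the per-protocol set, and its mITT definition asks only for a pre-measurement. Under section 2.8 the patient stays in the primary analysis; under section 2.4 it is open whether there is a week-12 value to analyse.

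**The case against.** The strongest defence concerns the main sample. The two rates describe different losses: the 40% is tied to the per-protocol analysis, while the 20% is applied to the primary analysis model, whose population is mITT. Low attenders are not excluded from mITT, so 140 × 0.6 = 84 estimates the per-protocol set and not the primary one. This stands. The documents do not show that 40% of primary outcomes will be missing, and one 40% rate should not be imposed on both calculations. What remains is that the article never draws this distinction, calls the 40% a drop-out rate, and in section 2.4 uses the same term for low attendance.

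A reader might go further and infer that the main trial is underpowered, with 84 evaluable against 111 and power falling to about 64%. The documents do not support that. The 64% arises only with 10 numerator df, a setting the article does not state and which does not fit a two-group contrast. With 1 df, 84 patients still give about 95%.

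For the sub-sample, it can fairly be said that the gap is only 2 or 3 patients, that the rate is given as approximate, and that the target of 44 is itself doubtful. All of this limits the weight of the point. None of it makes 42 meet a minimum of 44.

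**Conclusion.** The point holds in two limited parts.

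1. The sub-sample statement is wrong as written: 42 expected evaluable (41 at the exact predecessor rate) against a stated minimum of 44. The shortfall is 2 to 3 patients, and it disappears only if drop-out is 37.1% or less. This rests entirely on the article's own figures. The detectable differences in the working also assume a 1-df two-group ANCOVA with five covariates.
2. The 20% and 40% rates are not reconciled. They are compatible if 20% is missing week-12 BBS in the mITT set and about 40% is loss to the per-protocol set, but the article does not say so, and sections 2.4 and 2.8 treat low attendance differently.

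No loss of main-trial power is claimed. The consequence is a published justification that contradicts itself and an ambiguity about who contributes a primary outcome. Both should be corrected.

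**What to change.** 1. **Sub-sample.** Replace the statement that 70 is sufficient with the expected 42 evaluable (41 at 41.4%). State what that number detects at the alpha of 1% already chosen: d of about 1.11 at 80% power or about 1.37 at 95%, for a 1-df ANCOVA. Correct the base of 44 and its error df in the same edit, since neither follows from f = 1.47 with a 1-df test.
2. **Loss rates.** Define the 20% as missing week-12 BBS in the mITT set and the figure of about 40% as loss to the per-protocol set. Say that the per-protocol sensitivity analysis can then expect about 84 of 140.
3. **Attendance rule.** Reconcile sections 2.4 and 2.8 so that it is explicit that patients with fewer than 9 sessions still have their outcomes assessed, remain in the mITT analysis, and leave only the per-protocol set. This concerns outcome collection and analysis, not treatment.

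The cost is a few restated figures and sentences, plus post and follow-up assessments for low attenders if these are not already intended. No additional enrolment is needed.

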## Methods

2

The aim of the current MS-HIPPO II study is to quantify the effects of hippotherapy on balance control in MS patients by means of state-of-the-art biomechanical and neurophysiological measurements. The effects of hippotherapy will be assessed in a larger number of cases (N = 140), on evidence level 1b via an RCT study design, also including a follow-up measurement. The follow-up assessment is intended to provide information on the persistence of potential effects.

The outcome measures used in the first MS-HIPPO study will be extended in this study to biomechanical, as well as neurophysiological measurements, such as cortical activity, during balance and balance perturbation tasks [14]. The primary hypothesis to be tested is:(1)Twelve units of hippotherapy significantly changes static balance performance, measured with the Berg Balance Scale (BBS) and a force plate, in the intervention group compared to the control group. Moreover, this change can also be sustained after the end of the intervention period (follow-up).

Secondary hypotheses are:(2)Hippotherapy significantly changes the neuronal correlates of balance performance, measured with electroencephalography, in the intervention group compared to the control group.(3)Hippotherapy leads to a change in MS specific symptoms such as spasticity, fatigue and pain in the intervention compared to the control group. Moreover, it is also expected that hippotherapy will positively influence motor functioning parameters, quality of life and participation in the intervention compared to the control group.

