The balance perturbation task will be performed on an oscillating sensorimotor therapy device (Bioswing Posturomed®, Haider, Pullenreuth, Germany) [20]. The task consists of reactive balance control after a previous balance perturbation (with manual triggering of the oscillating movements (see Table 6)). The oscillating mechanism enables dosed, damped pendulum movements with standardized oscillation amplitudes and frequencies (perturbations) [20]. The stabilization behavior is recorded by an acceleration sensor (3D Acceleration Sensor, Brain Products GmbH, Gilching, Germany). With regard to the attainment of postural stability, the postural corrective information from the start of movement of the platform, shall be calculated via the accelerometer data. During the balance perturbation task, perturbation-evoked cortical potentials will also be recorded via EEG.

In regard to technical specifications, the AccuGait-Optimized force plate (Advanced Mechanical Technology, Inc., Massachusetts, US), provides a measuring accuracy of .01 % according to the manufacturer, and is CE-certified [21]. Based on precision grid calibration technology, measurement accuracy is secured (10 separate force values for 400 locations on the platform surface) [21]. AMTI Balance Clinic measurement software will be used for data processing (Advanced Mechanical Technology, Inc., Massachusetts, US version, 1.5.0). Measures of CoP (average, range, standard deviation, path length, 95th percentile ellipse measure, velocity) will be calculated. The sampling rate will be 50 data sets per second, filtered with a fixed 100 Hz third-order analog filter. Three valid trials per condition will be collected, which is consistent with current methodological practice to maximize the reliability of CoP-based balance measures in neurological populations and minimize the risk for distort CoP outcomes due to fatigue [[22], [23], [24], [25]]. The number and duration of tasks and trials are specified in Table 6. The EEG system LiveAmp 32 and actiCAP slim/snap (Brain Products GmbH, Gilching, Germany) fulfills the requirements of Medical Device Directive 93/42/EEC (MDD), classification DIN EN 62304, class 1 [26]. Bioswing Posturomed® diagnostic device (Haider, Pullenreuth, Germany) is certified according to MDR 2017/745 class I medical device [20].

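### The 95% power stated for the biomechanical/EEG sub-sample is derived from the Berg Balance Scale, so it is not supported for the force-plate, Posturomed or EEG outcomes

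*Protocol article*

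**What the plan says.** Section 2.8 (Statistical procedures) contains two sample size calculations.

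- **Whole trial.** The BBS is the primary outcome measure. An ANCOVA with two groups, five covariates, f = .40, alpha .05 and power .80 gives N = 111, raised to 140 for 20% attrition.
- **Sub-sample.** For the experimental protocol, "a reduced sample size was calculated on the basis of the effect strength of the preliminary study". The input is "the mean difference in BBS of 3.07 points (standard deviation (SD) = 1.04) of the IG and CG", with "95 % CI: 1.00–5.14, p = .004". The levels are "a type 1 error rate of α = 1 % and a power of 1-β = 95"%, the assumed effect is f = 1.47 and the result is N = 44 (df = 36, actual power .95). Allowing for about 40% loss (41 of 70 in the predecessor's per-protocol set), "a total of 70 patients (2x35) shall be randomized for in depth-biomechanical and neurophysiological measurements". The article says this secures enough cases for the more extensive analysis.

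The outcomes specific to this protocol are in section 2.5. For the force plate, "Measures of CoP (average, range, standard deviation, path length, 95th percentile ellipse measure, velocity) will be calculated". EEG band activity, perturbation-evoked potentials and Posturomed stabilisation are added to these. Section 2 (Methods) states hypothesis 2 as "Hippotherapy significantly changes the neuronal correlates of balance performance, measured with electroencephalography, in the intervention group compared to the control group" and names the force plate next to the BBS in primary hypothesis 1. It also says that the biomechanical and neurophysiological measures extend those of the predecessor trial.

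**The concern.** A power statement belongs to one test on one outcome. The BBS is scheduled for every patient and has its own calculation, so it needs no sub-sample. The sub-sample is there for the CoP, Posturomed and EEG measures, but the only effect used to size it is a BBS effect. The article does not argue that a BBS effect of that standardised size carries over to CoP or EEG. Since these measures are described as an extension of the predecessor's, the article also points to no source there for their effect or SD.

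At stake is how firmly hypothesis 2 and the force-plate part of hypothesis 1 can be presented. A reader of section 2.8 will take it that the extended analysis was sized at 95% power and alpha 1%. That was never worked out for those outcomes.

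**Working it through.** **Inputs, all from section 2.8:** difference 3.07; SD as labelled 1.04; f = 1.47; alpha .01; power .95; two groups; five covariates; N = 44; 70 randomised; about 40% loss. The main calculation supplies 20% attrition and f = .40 as its large effect.

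**Step 1: where f comes from.** For two equal groups f = (difference/SD)/2 = (3.07/1.04)/2 = 2.952/2 = 1.476. This is the stated 1.47, so the effect size rests on BBS figures alone.

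**Step 2: the plan's N.** The test is a noncentral F with lambda = f² × N, numerator df 1 (two-group effect) and error df N − 2 − 5 = N − 7. With f = 1.47 and alpha .01, N = 15 already gives power .968, and N = 44 gives power above .999. Numerator df up to 10 brings the required N to no more than 27. N = 44 is reached only near numerator df 40, which does not fit two groups. The error df would be 44 − 7 = 37, not 36. The stated N = 44 therefore does not reproduce from the stated inputs. Under the two-group test, 44 patients at 95% power correspond to f = 0.667.

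**Step 3: the loss allowance.** 70 × 0.6 = 42, below 44; 44/0.6 = 73.3, so 74 would be needed.

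**Step 4: detectable effect for the sub-sample's own outcomes.** The same F-test is solved for f. The number evaluable is not stated, so a range is used: 40% loss (70 × 0.6 = 42), 20% loss (70 × 0.8 = 56) and no loss (70).

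| Evaluable | f for 80% power, alpha .05 | f for 95% power, alpha .01 |
|---|---|---|
| 42 | 0.445 | 0.684 |
| 56 | 0.382 | 0.584 |
| 70 | 0.340 | 0.518 |

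Here f is on the covariate-adjusted scale (half the arm difference divided by the residual SD). A baseline–post correlation would lower the raw standardised difference required. The article gives no such correlation.

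**Step 5: power under assumed effects.** The article gives no CoP, Posturomed or EEG effect, so f is an assumption.

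| Assumed f | Alpha .01: N = 42 / 56 / 70 | Alpha .05: N = 42 / 56 / 70 |
|---|---|---|
| .25 | .15 / .22 / .30 | .35 / .45 / .54 |
| .40 | .46 / .62 / .75 | .71 / .84 / .91 |
| .50 | .70 / .85 / .93 | .88 / .96 / .99 |

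At the stated alpha of 1%, none of these reaches 95%, even with no loss. At alpha .05 the larger effects do reach it with 56 or more patients.

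**Side check on 1.04.** The interval half-width is (5.14 − 1.00)/2 = 2.07, and 2.07/1.04 = 1.99. The ratio 3.07/1.04 = 2.95, read as a t value, gives p of about .004, as printed. So 1.04 behaves like a standard error. That is a separate fault: a corrected BBS SD would still belong to an outcome the sub-sample was not created for.

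**The case against.** The strongest defence is that the proxy is disclosed. Section 2.8 names the BBS in the same sentence and never attaches 95% power to a named EEG, CoP or Posturomed test. No better input is visible in the article, and the force plate measures the same construct, static balance. The protocol for the sub-sample is called experimental and EEG is a secondary hypothesis, so neither needs a power calculation of its own. All of that stands. An exploratory sub-sample with no power claim would raise no objection. But the article does print alpha, power and a minimum N, presents the result as sufficient for the extended analysis, words hypothesis 2 as a significance claim and puts the force plate in the primary hypothesis.

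It is also fair that 42 is the pessimistic end. The 40% loss comes from a per-protocol set, whereas the modified intention-to-treat set is primary here and the main calculation assumes 20%. The range in the working reflects this. The 1% level appears only in the sizing; the primary ANCOVA is planned with a 95% interval, so the alpha .05 figures are the more relevant ones.

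A reader might infer three stronger things that the documents do not support:

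- That the sub-sample is underpowered. Without a CoP or EEG effect or SD, the true power cannot be computed in either direction.
- That only very large effects are detectable. That depends on the number evaluable, the alpha level and the unknown covariate adjustment.
- That a null result will be read as proof of no effect. No such interpretation is planned anywhere in the article.

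**Conclusion.** The point holds as a fault in what section 2.8 states, not as proof that 70 patients are too few. The 95% power at alpha 1% rests on a BBS effect alone. It is therefore unsupported for hypothesis 2, for the force-plate part of hypothesis 1 and for the Posturomed outcomes. What the sub-sample can detect with 80% power at alpha .05 is f of about 0.34 to 0.445, depending on loss between 0% and 40%. Reaching the stated 95% at alpha 1% would take f of about 0.52 to 0.68. These figures assume equal groups, a single two-group contrast, five covariate degrees of freedom and effects on the covariate-adjusted scale. The BBS analysis in the full trial is not affected.

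**What to change.** 1. In section 2.8, remove the claim of 95% power at alpha 1% for the sub-sample and describe 70 as a feasibility number.
2. State the detectable effect in its place. For example: for the two-group ANCOVA with five covariates, 80% power at two-sided alpha .05 requires f of about 0.445, 0.382 or 0.340 with 42, 56 or 70 evaluable patients, on the covariate-adjusted scale.
3. Report CoP, Posturomed and EEG arm differences with confidence intervals as exploratory, and say that a non-significant result will not be taken as absence of effect.
4. Align the hypotheses in section 2. Make the BBS alone the primary hypothesis test, as section 2.5 already makes it the primary outcome measure, and place force plate and EEG as secondary or exploratory. Without this step, item 3 would contradict primary hypothesis 1.
5. Reconcile Table 7, which lists the balance/EEG assessment at all three visits without restricting it to the sub-sample, with section 2.8, which adds the force-plate and Posturomed tasks for the sub-sample.

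The cost is wording in sections 2, 2.7 and 2.8 and in any analysis plan, a less favourable stated power and a weaker status for hypothesis 2. No extra patients are needed.
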